### Setting

This study will be conducted at Public Health Centers (PHCs) in Yogyakarta city. Yogyakarta city is one of the 5 districts in Yogyakarta Special Region Province. It has an area of 32.5 km2 (1,02% of the total Yogyakarta province area) and a population of 416,041 people in 2019. It is divided into 14 sub-districts. Every sub-district has 1 to 2 PHCs with a total number are 18 PHCs in Yogyakarta city [21]. Each PHC has a program to engage patients with chronical diseases in the disease treatment. The program is called program pengelolaan penyakit kronis shortened to “PROLANIS” which has 58–165 members with the same characteristics in all PHCs. PROLANIS could roughly translated as chronical disease management program.

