Phase 1 (Qualitative study). The Focus Group Discussions (FGD) and in-depth interviews will be conducted for data collection. Participants will be divided into three groups, patients with T2DM, families and nurses group. Ten PHCs will be randomly selected, and participants will be selected by the person in charge in PROLANIS at each PHC according to the inclusion criteria. FGDs will be conducted to determine knowledge, abilities, barriers and needs of Patients with T2DM, families and nurses in carrying out diabetes self-management referring to the pillars of DM management. Specifically this phase will investigate targeted user’s need in using a mobile application. Patients with T2DM and families will be reached by staffs visiting their homes and being followed up by phonecall. The FGD will be held for approximately 60 minutes online using zoom video conference platform. It will be guided by researcher and assisted by two nurses with master’s degree qualification who act as note taker and observer. Gender, religion, and socioeconomic status are highly considered when we form the FGD groups to ensure that participants will feel comfortable expressing their unique experiences during the FGD process. We will triangulate the data collection by reviewing evidences from other sources to get accurate data. In-depth interviews will be conducted with 10 physicians who treats patients with T2DM at the PHC in Yogyakarta and are in charge at PROLANIS and 2 staffs in charge at the Health Social Security Agency namely [Badan Penyelenggara Jaminan Sosial Kesehatan (BPJS Health)] until data saturation is reached. The interview will be conducted by the researcher for 45–60 minutes in a closed room at PHC. Participant recruitment is determined by the person in charge of PROLANIS from the PHC. Participants will be given an explanation about the study and asked to complete informed consent forms for approval and willingness to participate in the study before the FGD and interviews are started. The FGD and interview guidelines were made based on references to self-management and the pillars of DM management. The FGD will be recorded using zoom recorder and interviews will be recorded using an audio recorder. FGD responses and interviews will be compiled in verbatim transcripts. Peer debriefing and member checking will be done to increase the trustworthiness of the data. We will ensure credibility by doing triangulation of methods (conducting FGD and interviews) and data sources (involving data from patients, families, nurses and physicians. To ensure transferability in this study we will later provide detail, clear, and systematic description of the research results.

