Phase 3 (Quantitative study). This phase will use a non-equivalent control group design, which applies a pre-repeated post test control group design. Participants in this phase are Patients with T2DM, family caregivers, and nurses according to the inclusion criteria. The experiment and control group are determined by the person in charge of PROLANIS at PHC based on geographic location and PROLANIS activity evaluation data. Data collection will be conducted at two PHCs which has the lowest patients with T2DM number of visits based on data from BPJS Health. However, if the number is not sufficient, it will expand to other PHC. The experiment group will be given IDSM Application, and the control group will use the whatsapp group to communicate or consult directly with a health provider. Self-management will be carried out independently by the patient in his or her home. Monitoring by a health provider will be carried out using whatsapp group and when patient come to the PHC for routine check up. Determination of research subjects will be done by consecutive sampling on patients with T2DM. The sample size was calculated based on the formula for calculating sample size from Lemeshow by considering the hypothesis test for two populations means “two sided” test, with α = 5%; Z(1-α) = 1.96; β = 20%; Z(1-β) = 0,84, standard deviation = 0,9 with mean difference = 0.6 [26], then the calculation of the sample size is obtained n1 = n2 = 35 participants. To anticipate the possibility of participants dropping out, a number of samples will be added to keep them fulfilled by the formula: n’ = n/(1-f) [27]. As a result, four participants will be added so the number of samples needed is n1 = n2 = 39 participants. The sample will be divided into two groups, each group consisting of 39 patients with T2DM included in the experiment group and 39 Patients with T2DM included in the control group. The sample will be selected according to the inclusion criteria.

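### If each PHC forms one arm, as the Phase 3 text most naturally reads, the 80% power and 5% error computed for independent patients are not delivered

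*Protocol article*

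**What the plan says.** All of this is in the Protocol article. Under *Study phases and data collection*, Phase 3 is declared a non-equivalent control group design. The experiment and control groups are "determined by the person in charge of PROLANIS at PHC based on geographic location and PROLANIS activity evaluation data". On sites it says: "Data collection will be conducted at two PHCs which has the lowest patients with T2DM number of visits based on data from BPJS Health". The next sentence allows expansion to other PHCs if numbers are insufficient, without saying how many or to which arm they would go.

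The sample size rests on "considering the hypothesis test for two populations means", two-sided, "with α = 5%; Z(1-α) = 1.96; β = 20%; Z(1-β) = 0,84", with standard deviation 0.9 and mean difference 0.6: "then the calculation of the sample size is obtained n1 = n2 = 35 participants". Dropout is the only inflation, giving 39 per arm.

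Under *Data analysis*, HbA1c is compared between groups after the intervention by an independent t-test or Mann-Whitney test. Self-management is compared by a summary measure or Mann-Whitney test. Multiple regression is planned to find the most influential variables, not to adjust the between-arm comparison. PHC appears in none of these analyses.

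Under *Setting*, PROLANIS is described "with a total number are 18 PHCs in Yogyakarta city", and its members are said to have the same characteristics everywhere.

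**The concern.** Two PHCs, with groups set partly by location, most naturally means that one PHC receives the app and the other does not. Everything else that differs between the two PHCs (nurses, physicians, intensity of the programme) then falls wholly on one arm. Staff contact is part of the comparison itself, because control patients consult their provider through a messaging group. The assignment also draws on programme evaluation data, which may be related to how patients would fare without the app.

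Two consequences follow. Any PHC difference over the three months would be reported as an app effect. The standard error of a patient-level test also leaves out between-PHC variation, so p-values are too small and the stated power is too high. Effectiveness is the main aim under *Study aims*, and the results are meant to inform the health insurer under *Dissemination and implementation*.

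**Working it through.** **Inputs from the protocol.** Two-sided 5% (1.96), power 80% (0.84), SD 0.9, difference 0.6, 35 evaluable and 39 enrolled per arm, two PHCs. **Assumed.** The intracluster correlation (ICC), which the protocol does not give; 0.005 to 0.05 is used as a range.

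**1. The plan's own figure.** n per arm = 2 × [0.9 × (1.96 + 0.84) / 0.6]² = 2 × 4.2² = 35.28, stated as 35. Four extra patients correspond to about 10% dropout: 35 / 0.90 = 38.9, so 39. With 35 per arm, SE = 0.9 × √(2/35) = 0.215 and power = Φ(0.6/0.215 − 1.96) = 79.6%. The arithmetic is sound if patients are independent.

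**2. One PHC per arm.** With m = 35 patients per PHC:
- design effect DE = 1 + 34 × ICC
- effective n per arm = 35 / DE
- type I error of the planned test = 2 × [1 − Φ(1.96/√DE)]
- power at a true 5% level = Φ(0.6 / (0.215 × √DE) − 1.96)

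| ICC (assumed) | DE | Effective n per arm | Type I error, planned test | Power at true 5% |
|---|---|---|---|---|
| 0.005 | 1.17 | 29.9 | 7.0% | 73% |
| 0.01 | 1.34 | 26.1 | 9.0% | 67% |
| 0.02 | 1.68 | 20.8 | 13.0% | 58% |
| 0.05 | 2.70 | 13.0 | 23.3% | 40% |

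Simulating the planned t-test (40,000 runs each) gave type I errors of 9.2%, 13.4% and 23.9% at ICC 0.01, 0.02 and 0.05.

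The power column treats the ICC as known. With one PHC per arm there are zero between-PHC degrees of freedom, so the trial cannot estimate it. Even with a known ICC, above 1/35.3 = 0.028 no number of patients in two PHCs reaches 80%.

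**3. The same point without an ICC.** Suppose the two PHCs differ by 0.2 for reasons unrelated to the app. The planned test then rejects with probability about Φ(0.2/0.215 − 1.96) + Φ(−0.2/0.215 − 1.96) = 15% when the app does nothing.

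**4. If expansion gives two PHCs per arm.** m = 17.5, ICC 0.02: DE = 1 + 16.5 × 0.02 = 1.33, type I error 8.9%, power 68% (ICC again treated as known).

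**5. The same number of patients over more PHCs.** Five PHCs per arm, 7 evaluable each, ICC 0.02: DE = 1 + 6 × 0.02 = 1.12. Use a t-test on PHC means with 8 degrees of freedom. Baseline adjustment at correlation r multiplies the SD by √(1 − r²), here taken to leave the ICC unchanged.

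| r (assumed) | SE | Power, 5 PHCs per arm | One PHC per arm, ICC treated as known |
|---|---|---|---|
| 0 | 0.228 | 64% | 58% |
| 0.5 | 0.197 | 76% | 70% |
| 0.7 | 0.163 | 90% | 85% |

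Most of the gain in power comes from baseline adjustment. Several PHCs per arm add something different: the PHC component can be estimated, which the last column takes for granted and one PHC per arm cannot supply.

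**The case against.** **The allocation unit is an inference.** The text never says that each PHC is one arm, the data collection flow (Fig 2) is not available here, and expansion to other PHCs is allowed. If both arms were formed inside each PHC, the inflation in step 2 would largely go. This stands, and the error and power figures are conditional on it. It does not clear the plan. Groups chosen by staff and compared on unadjusted post-intervention values still do not assure a 5% error, and step 4 shows that a modest expansion falls short too.

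**The ICC is assumed.** This also stands: the size is a range. The direction holds for any positive ICC. The statement that PROLANIS members are alike in all PHCs comes without data, and similar patients do not imply similar staff or care.

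**Non-random allocation is declared.** It is, with a commitment to the TREND checklist under *Security and data management plans*. A reader might infer that the plan is at fault for not being randomised, or that PHCs must be assigned by lot. The protocol does not support that inference. It chose a non-equivalent design openly, and with only two PHCs a draw would leave app and PHC just as inseparable. Declaring the design does not, however, make a power calculation for independent patients valid.

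**Conclusion.** The point holds conditionally. If arm follows PHC, the planned comparison does not have 80% power and 5% error. For an assumed ICC of 0.005 to 0.05, type I error is about 7% to 23% and power at a true 5% level about 73% to 40%. With one PHC per arm, the app effect cannot be separated from the PHC effect, and more patients at the same two PHCs would not change that. If both arms sit within each PHC, the clustering loss is small, but staff selection and the lack of baseline adjustment remain.

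A reader might also infer that spreading the patients over more PHCs would give 90% power at no cost. The documents do not support this: 90% needs a baseline correlation of 0.7, which appears nowhere in them, and the unadjusted figure is 64%.

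**What to change.** 1. State the unit of allocation in Phase 3, and to which arm any added PHC would belong.
2. If the unit is the PHC, replace the 80%/5% statement with power and type I error over a stated ICC range, as in step 2.
3. Adjust the between-arm comparisons for the baseline HbA1c and self-management values, which are already collected. Do this under either allocation scheme.
4. If one PHC per arm is kept, state that the comparison is exploratory and cannot separate the app from the PHC.
5. Where feasible, recruit the same 78 patients from several PHCs per arm and include PHC in the analysis, with degrees of freedom suited to few PHCs. The city has 18, and for Phase 1 "Ten PHCs will be randomly selected". Report the resulting power over ranges of ICC and baseline correlation; it may still be below 80%.

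Items 1 to 4 need no new patients or measurements. They cost a revised sample size paragraph, one change to the analysis and a more cautious conclusion. Item 5 adds coordination and app training at more PHCs.

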**Fig 2 pone.0277127.g002:**
[figure not shown]
The quasi-experiment data collection flow.

### Study population

#### Inclusion, exclusion, and withdrawal criteria of participants

Phase 1 (Qualitative study). Participants will be determined using maximum variation purposive sampling technique with the following inclusion and exclusion criteria: 1) Patients with T2DM who is willing to be participant, member of PROLANIS, aged 21 years old or older [30], diagnosed with T2DM for at least 1 year, has a smartphone and can operate it. Exclusion criteria are: patients with Type 1 Diabetes Mellitus (T1DM) or participant who have history of diabetes since childhood, Patients with T2DM who are pregnant, who have comorbidities with Chronic Kidney Disease (CKD), or mental disorders; 2) Family caregivers inclusion criteria are: members of family aged 18 years old and older, family members who live in the same house as the patient, have a smartphone and can operate it. Exclusion criteria are: family members who work outside the home full day, family members with DM, family members who have mental disorders or who are sick; 3) Nurses: a nurse who carry out the PROLANIS program at PHC where they are on duty, has a smartphone and can operate it. Exclusion criteria are: nurses who are on leave from work; 4) Physician: a physician who treats patients with T2DM at the PHCs in Yogyakarta City and are in charge in PROLANIS. Exclusion criteria are on leave from work; and 5) For BPJS Health Officers: a staff who manages and is responsible for the PROLANIS program within the scope of BPJS Health. Exclusion criteria are: officers who are on leave from work and officers who are conducting tasks out of town.

Phase 2 (Qualitative study). For the HE method, participants are experts who have experience in the field of computer science or digital health and understand the heuristic principles. For the TA method, participants who will be involved are patients diagnosed with T2DM for at least 1 year, aged 21 years old or older and are members of PROLANIS, family caregiver members who live at home. For the nurse: nurses who carry out the PROLANIS program and has a smartphone and can operate android-based applications.

Phase 3, (Quantitative study). The participants to be recruited are: 1) Patients with T2DM: willing to be participant, member of PROLANIS, aged 21 years old or older, diagnosed with T2DM for at least 1 year, has a smartphone and can operate it. Exclusion criteria are: patients with T1DM or participant who have history of diabetes since childhood, patients with T2DM who are pregnant, have comorbidities with CKD, or have mental disorders; 2) For family: family caregiver aged 18 years old and over, family members who live in the same house as the patient, have a smartphone and can operate it. Exclusion criteria are: family members who work outside the home full day, with mental disorders or who are sick; 3) For nurses: a nurse who carry out the PROLANIS program at PHC where they are on duty and has a smartphone and can operate it. Exclusion criteria are: nurses who are on leave from work. Withdrawal criteria are: Patients with T2DM who withdrew, who had to be hospitalized, did not complete self-management results in first, second and third months, or did not follow HbA1C measurements before and after the intervention.

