
Phase 2 (Qualitative study). Phase 2 is focusing on the apps testing. A Heuristic Evaluation (HE) technique will be conducted to ensure that the user interface and user experience of the apps are meeting all heuristic principles. HE is a usability testing that is needed before the application is used. Three experts who have experience in the field of computer science or digital health and understand the heuristic principles will conduct the evaluation in two rounds will be involved in two rounds [22, 23]. In the first round, each expert will conduct the evaluation independently. They will be asked to use the apps and note any violation on heuristic principles they found and rate each violation by 1 (cosmetic problem) to 4 (catastrophe). The apps’ module will be provided as wellas a Heuristic principles checklist. In the second round, after the evaluation is complete, a meeting will be arranged to discuss the identified heuristic problems and any disagreement among the experts. The result of the second round will be consensus on the heuristic problem and the rates.

The second technique is a Think Aloud (TA) method will be used to find any problem in the IDSM App. Participants in this phase are Patients with T2DM, families and nurses who were involved in the phase 1. Five participants in each group will be randomly selected [24]. They will be given an explanation and a consent form before the trial started. The TA method is based on the participants’ treatment-related responses as indicated by body posture and speech when evaluating with an integrated diabetes management application. Participants will be given a task in accordance with their role. Participants will be asked to say what they are doing, seeing, and thinking while they are using the apps to complete the given task. All the behaviour and words said by the participants will be audio visually recorded. Including the screen of the app. The recording will be compiled into a verbatim transcript. The results of the transcript will be analysed to find problems in the operation of the application software carried out by users [25].

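### The Phase 3 criteria admit patients and family caregivers who took part in Phase 1 or 2, so a few previously exposed people can enter either arm; the expected effect is small and one exclusion line removes it.

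*Protocol article*

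**What the plan says.** All references are to the protocol article.

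- **Phase 1 sites and people** (Study phases and data collection): "Ten PHCs will be randomly selected, and participants will be selected by the person in charge in PROLANIS at each PHC". Setting gives the pool: "Every sub-district has 1 to 2 PHCs with a total number are 18 PHCs in Yogyakarta city". Patients, family members and nurses discuss self-management and what they need from an app. Expected results says the resulting themes supply the app's content.
- **Phase 2 think-aloud test** (same section): "Participants in this phase are Patients with T2DM, families and nurses who were involved in the phase 1". Five are drawn at random from each of the three groups, and they carry out set tasks in the app.
- **Phase 3 patients** (Inclusion, exclusion, and withdrawal criteria of participants): "willing to be participant, member of PROLANIS, aged 21 years old or older, diagnosed with T2DM for at least 1 year", with a smartphone that they can operate. Excluded are type 1 or childhood-onset diabetes and "patients with T2DM who are pregnant, have comorbidities with CKD, or have mental disorders". Family and nurse criteria and withdrawal criteria follow. Earlier participation is not mentioned in any of them.
- **Phase 1 patients** (same section) meet the same conditions, including "diagnosed with T2DM for at least 1 year, has a smartphone and can operate it".
- **Phase 3 sites and sampling** (Study phases and data collection): the two health centres (PHCs) with the fewest visits by patients with type 2 diabetes, with others added if numbers fall short. Sampling is consecutive, and the person in charge of PROLANIS determines the groups.

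**The concern.** Phase 3 is the only comparative part of the study, and its baseline is meant to describe patients before they meet the intervention. A think-aloud tester has already used the app. A discussion participant has already spent a session on self-management, which is the subject of one of the two measured outcomes. The same may apply to a patient whose family caregiver took part. As written, all of them qualify.

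Allocation is not random and sampling is consecutive, so nothing in the design balances earlier exposure between the arms. The direction of any bias depends on where these people land. If earlier exposure helped, an exposed control shrinks the between-group difference. An exposed patient in the app arm may add to a comparison of post-intervention values, yet show a smaller before-after change because the starting score is already raised. Data analysis lists age, diabetes duration, gender, education and profession as descriptive characteristics, and none of these would reveal the overlap.

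**Working it through.** **1. Does the text admit earlier participants?** Set the two patient lists side by side.

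| Condition | Phase 1 | Phase 3 |
|---|---|---|
| Willing, PROLANIS member | yes | yes |
| Age 21 or over | yes | yes |
| Type 2 diabetes for at least 1 year | yes | yes |
| Has and can operate a smartphone | yes | yes |
| Excluded: type 1 or childhood onset, pregnancy, CKD, mental disorder | yes | yes |
| Excluded: took part in an earlier phase | – | not listed |

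A patient who met the Phase 1 list and whose condition has not changed meets the Phase 3 list. The Phase 3 family list likewise has no exclusion for earlier participation.

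**2. The plan's own sample size.** Inputs from Study phases and data collection: SD 0.9, difference 0.6, z = 1.96 and 0.84.

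n per group = 2 × (0.9 × (1.96 + 0.84) / 0.6)² = 2 × 4.2² = 35.28. The article states 35; rounding up gives 36. With 10% dropout (assumed, as the article does not give f), 35 / 0.9 = 38.9, so 39 as stated. Two-sided t-test power with 35 per group is 78.5% (79.6% by the normal approximation). The figures below use the t-test.

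**3. Expected number of patient testers at the Phase 3 centres.** Inputs: five patient testers, 18 PHCs, two Phase 3 PHCs. Assume that each tester is equally likely to come from any of the 18, and that being a low-visit centre is unrelated to the random Phase 1 draw.

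5 × 2/18 = 0.56 across both centres. If each arm is one centre (an assumption), that is 5 × 1/18 = 0.28 in the control centre. These count testers who belong to the centres, so the number who enrol is no larger.

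**4. Effect on power if exposed people are controls.** Assume, as an extreme, that each exposed control already has the whole 0.6 benefit. With k exposed among 39 enrolled, the difference becomes 0.6 × (1 − k/39). Power is taken at 35 analysed per group, assuming that dropout is unrelated to exposure.

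| k exposed controls | Difference | Power |
|---|---|---|
| 0 | 0.600 | 78.5% |
| 0.28 (expected) | 0.596 | 77.9% |
| 1 | 0.585 | 76.4% |

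Dividing by 35 instead of 39 gives 0.583 and 76.1% for k = 1, which changes nothing of substance.

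**5. What cannot be computed.** The article does not give the number of discussion patients, so their contribution cannot be sized. Nor does it give any figure for how far one discussion or one test session moves the self-management score or HbA1c.

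**The case against.** The strongest reply is that this is one missing line in a condensed article. Nothing says that earlier participants will be enrolled, the Phase 3 flow figure is not available, and the full protocol may exclude them. That has some weight. But the article does set out inclusion, exclusion and withdrawal criteria for Phase 3 at length and for each type of participant, and applied as written they let these people in. That makes it more than an unprinted detail.

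The second reply is about size, and it largely stands. Phase 1 is an online discussion of about an hour, held before the app exists. Phase 2 is an observed task session, and no continued access to the app is described. A full three-month benefit from either is not credible, so the table above overstates the loss for each exposed control.

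Three stronger readings are tempting, and the article does not support them.

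- *Contamination is likely because the sites overlap.* With 10 of 18 PHCs in Phase 1, the chance that at least one of two Phase 3 PHCs was among them is 1 − 28/153 = 82%. That is the probability that a centre is shared. It says nothing about how many Phase 3 patients were exposed, since sharing a centre with a discussion participant exposes no one else.
- *Power falls to 67%.* This needs all five patient testers to be enrolled as controls, each with the full benefit: 0.6 × (1 − 5/39) = 0.523. The expected number in a control centre is 0.28.
- *A nurse who tested the app could influence a whole control centre, or testers arrive already trained and motivated.* The article gives no route for the first, because controls receive a WhatsApp group and e-modules. The think-aloud session looks for usability faults and does not teach. Every app-arm patient is trained before use anyway.

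**Conclusion.** The point holds in a limited form. The Phase 3 criteria admit patients and family caregivers from Phases 1 and 2 to either arm, and for those patients the baseline self-management score may not be a pre-exposure value. The expected number of patient testers is about 0.56 across the two Phase 3 centres, plus an unknown number of discussion participants. One control with the full benefit would cost about two percentage points of power (78.5% to 76.4%); the expected 0.28 would cost about 0.6 of a point (78.5% to 77.9%). The net direction cannot be stated in advance.

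This rests on testers being spread evenly over the 18 centres, one centre per arm, and the 0.6 and 0.9 used for the sample size. If the discussion groups turn out to be large and concentrated in the Phase 3 centres, more people would be affected, though each would have had only the discussion and no app use. It is a minor, avoidable source of bias and does not threaten the trial's conclusion.

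**What to change.** Add one sentence to the Phase 3 exclusion criteria: *Patients who took part in Phase 1 or 2, or whose family caregiver did, are not eligible for Phase 3.*

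The cost is a handful of otherwise eligible patients. Setting gives each centre's programme as one "which has 58–165 members with the same characteristics in all PHCs", and each arm needs 39. If an arm came wholly from a centre of the smallest size, 58 − 39 = 19 members would remain, not all of them necessarily eligible, so losing a few could matter there. The article already allows recruitment to extend to other centres if numbers fall short.

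No change to how Phase 1 centres are chosen is needed. Drawing Phase 1 only from other centres would take the low-visit centres out of the needs assessment. Nor is a rule on where nurse testers work needed: barring their centres only as control sites would leave them open as app sites and permit the opposite imbalance.
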